***Study Setting***

***Kenya :*** The Kenyan site for the ARMADILLO stage 2 will be Kwale County. Kwale County is one of the six counties in the Coastal region of Kenya. The total population of Kwale County was projected to be 713,487 persons in 2012 comprising of 346,898 males and 366,589 females. This is a 9.8% increase from 649,931 in 2009 national census. The County population growth rate is 3.1% and the sex ratio is 95 males per 100 female. Those <15 years of age in 2012 constituted 47.23% of the entire population. 19.0% of the entire population in Kwale County constituted of young people aged 15-24 in the year 2012. The County’s total fertility rate is 6 children per woman(24). 49.0% of births are delivered at a health facility with the County having a contraceptive prevalence of 38.2% below the Country’s which is at 53.2%(25).

Age at first marriage as reported in KDHS 2014 for women in Kwale is 19.1 years while median age at first sexual intercourse for women was reported at 16.6 years and men 18.5 years . The County also has a high percentage rate of teenage pregnancies with 24.2% of women aged 15-19 having begun childbearing which is more than the Country’s average of 18%(26). In Kwale County 253,041 people have access to mobile phones of which 62,473 are in Kwale town, 72,865 are in Kinango and 117,703 are in Msambweni(27).

Prior to the start of the study, three geographically distant locations will be selected within Kwale County with the help of the Kenya National Bureau of Statistics (KNBS) as the Intervention, Contact and Control arms. The geographic distance will help reduce contamination.

***Peru:*** The study will take place in Peru, located in Western South America and home to about 31 million people. The country’s population is distributed across three geographic regions, the coast, the jungle and the highlands. This stage of ARMADILLO will take place in the capital city of Lima, on the coast of Peru and home to 9.8 million people or 31% of the population. About one-third of Peru’s adolescents live in Lima, with the highest proportions of youth living in peripheral areas similar to our study site(28).

The specific ARMADILLO study site will be Pampas de San Juan de Miraflores. Located in the southern cone of Lima, “Pampas” is one of the seven zones in the district of San Juan de Miraflores, which is one of Lima's 43 districts. Pampas' 46 human settlements (pueblos jóvenes) are home to approximately 50,000 residents(29). All participants in ARMADILLO will be recruited from Pampas.

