**Study Objectives:**

This research protocol will use an individually randomized design to assess differential learning related to sexual reproductive health and rights compared to those who are asked to learn on their own.

Primary Objective: To determine whether youth given access to ARMADILLO’s targeted SRH information through their mobile phones are more knowledgeable about contraception and better able to dispel contraception myths and misconceptions than those without access to ARMADILLO.

Secondary Objective: To determine whether youth given access to ARMADILLO’s SRH information through their mobile phones retain information on SRHR longer and more accurately than those without access to ARMADILLO.

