**Project description:**

***Study Design***

The study uses an individually-randomized, open three-arm comparative design to assess the objectives above. After obtaining written informed consent, individuals randomized to the ‘intervention’ arm of the ARMADILLO trial will receive access to ARMADILLO content over the course of the intervention and will use their mobile phones to access this content on demand. Those randomized to the ‘control’ arm will receive no intervention. Arm 3 will differ by site: in Kenya, those randomized to this ‘contact’ arm will be alerted to various SRH domains (e.g. health topics, including Relationships, Pregnancy, STIs, etc) and be encouraged to learn on their own; in Peru, those randomized to the ‘push’ arm will receive key messages daily with the option to learn more if they wish.

We have elected to include three arms, rather than the traditional ‘intervention’ and ‘control’ arms in an attempt to address lingering questions around the efficacy of informational digital health interventions in different settings. Across all arms, selected SRH outcomes will be assessed via a survey at baseline (prior to the intervention start), at intervention end, and at eight weeks (two months) following the end of the intervention. All outcomes of interest are linked to domains and content from the ARMADILLO system. Control group participants will receive no messaging, only assessments at baseline, and times corresponding to the intervention end and follow-up for the other two groups.

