***Data collection methods***

Prior to the start of the study, as part of a finalization of study tools, a number of Focus Group Discussions will be conducted in order to confirm young people’s key myths and misconceptions around contraceptive use, common reasons for not using contraception, as well as build an understanding of where young people access contraception and why. Additionally, in order to streamline the generic study questionnaire (which will assess participant learnings at baseline, end-intervention, and follow-up) to each site as well as ensure comprehension, necessity, and relevance of items for the different age groups being assessed, both Kenya and Peru will conduct a small pilot of the tool among 25-30 youth.

The selected methodology for the effect assessment involves a combination of close-ended surveys and in-depth interviews conducted in person, as well as short, spot assessments via mobile phone. All in-person study activities will take place in a private room at a location and time that is convenient. These rooms allow for both visual and auditory privacy. A project staff member will explain the study activity and answer any questions prior to and/or following completion of the given study activity.

In-person baseline assessment

All participants will complete a baseline, close-ended survey with questions linked to ARMADILLO content. The research team staff will then explain the participant’s expected interaction with the three arms to which they might be randomized and answer any questions. Participants will be told that, should they be randomized to intervention or Arm 3, they can be expect their first message from the system the following day. After the participant leaves, the participant will be randomly assigned to one of the three arms.

Study arms implementation

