Following enrolment, the phone number of each consented individual will be randomized into one of three arm using block randomization, with block sizes of 6, applied to the individual age-sex cohort lists. The process will continue until the sample size is achieved.

The allocation of participants into intervention, control, or Arm 3 groups (see Table 1 below) will be randomly determined but designed to achieve balance between the arms. Following enrolment of a participant into the study, an algorithm will determine to which study arm the participant’s phone number is subscribed. The subscription will be monitored either by the technology partner or a member of the research team not involved in enrolling participants. If allocated to the intervention arm or Arm 3, the participant will receive their first interaction from the appropriate system the following day. If allocated to the control arm, the participant will receive no interactions. Allocation to each arm based on the following characteristics will be assessed at least weekly to ensure balance: age, sex, and years of education.

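### The Kenyan study setting text makes three distant locations the three arms, contradicting individual randomisation; if carried out, it would tie each arm to one location

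*Protocol*

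**What the plan says.** For Kenya, the Study Setting section states that, before the study begins, three widely separated places in the county will be chosen "with the help of the Kenya National Bureau of Statistics (KNBS) as the Intervention, Contact and Control arms". It then gives the reason: "The geographic distance will help reduce contamination". It does not say that locations are assigned to arms at random.

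Other sections describe a different allocation:

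- Study Objectives: "This research protocol will use an individually randomized design".
- Study Design: "The study uses an individually-randomized, open three-arm comparative design to assess the objectives above".
- Data collection methods, on the baseline visit: "After the participant leaves, the participant will be randomly assigned to one of the three arms".
- Participants: randomisation follows the baseline survey, and a team member who has no contact with participants oversees the randomisation of phone numbers.
- Sampling strategy: "the phone number of each consented individual will be randomized into one of three arm using block randomization, with block sizes of 6", applied within age-sex cohorts. The same section counts 14 such cohorts for Kenya.

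None of these sections makes an exception for Kenya. Location is not among the strata, nor among the characteristics monitored for balance (age, sex and years of education). The Study sample size section gives no intracluster correlation or design effect. The Statistical analysis section names chi-square tests, t-tests and difference-in-difference, with multivariable regression if the arms turn out unbalanced. It names no location or cluster term.

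**The concern.** The two descriptions fix different units of allocation. Under one, a place is an arm. Under the other, each person in any place can fall into any arm. A Kenyan site team cannot follow both, and the protocol does not say which governs.

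The choice decides whether the Kenyan half of the study is a randomised comparison of individuals. Under the location version there is one cluster per arm, and anything that develops differently between the three places during the study is carried into the arm contrasts. Kenya's particular question, whether an effect comes from the message content or from mere contact, could not be separated from place. Staff recruiting in a given area would also know its arm, which defeats the separation of recruitment from allocation in the Participants and Sampling strategy sections. Participants who had been told at baseline that they might be randomised to any of three arms would have been told something untrue.

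This cannot be left to a statistical analysis plan. The protocol fixes the unit of allocation, and no analysis can repair one location per arm.

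**Working it through.** **Step 1. Can the Study Setting text be read harmlessly?** The harmless reading is three recruitment areas, each containing all arms. Two things speak against it. The text gives the locations the role of the arms. And the stated reason works only with one arm per location: if all three arms were recruited in each place, distance between places would not keep participants of different arms apart.

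**Step 2. Which version do Kenya's own numbers fit?** Inputs: 756 participants and 252 per arm (Study sample size), 14 cohorts and blocks of 6 (Sampling strategy).

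- 756 / 14 = 54 per age-sex cohort.
- 54 / 6 = 9 complete blocks.
- 54 / 3 = 18 per arm per cohort, and 18 x 14 = 252 per arm, as stated.

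The Kenyan total therefore reproduces exactly under individual block randomisation. The calculated 705 per site cannot be firmly reproduced, because no standard deviation, alpha or sidedness is given. This point does not depend on it.

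**Step 3. What could be estimated if locations were the arms?**

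- Degrees of freedom for location within arm: 3 locations - 3 arms = 0, at any sample size.
- A location term in the regression would be collinear with arm.
- Difference-in-difference subtracts each place's baseline level, so fixed additive differences drop out. A trend, event or response peculiar to one place remains, and cannot be told apart from an arm effect.

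**Step 4. Illustration of the error rate.** This applies to an endline-only comparison of two arms, one location each, with individuals treated as independent. Inputs: 252 per arm and dropout of up to 20% (Study sample size). Assumptions, not in the protocol: a two-sided 5% test, intracluster correlations (ICC) of 0.005, 0.01 and 0.05, and no systematic difference between places.

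- Completers per location: m = 252 x 0.8 = 201.6.
- Design effect: DE = 1 + (m - 1) x ICC.
- True type I error: 2 x (1 - Phi(1.96 / sqrt(DE))).

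| Assumed ICC | DE | True type I error |
| --- | --- | --- |
| 0.005 | 1 + 200.6 x 0.005 = 2.00 | 0.166 |
| 0.01 | 1 + 200.6 x 0.01 = 3.01 | 0.258 |
| 0.05 | 1 + 200.6 x 0.05 = 11.03 | 0.555 |

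**The case against.** The strongest reply is that the weight of the operational text lies with individual randomisation. Study Objectives, Study Design, Data collection methods, Participants and Sampling strategy all say so, the technology partner is to build a randomisation algorithm, and the Kenyan sample size fits it. If those sections govern, arm is not confounded with location, there is no design effect, and 756 stands. This is correct. A reader might infer from the Study Setting text that the Kenyan comparisons are confounded with place as a settled fact. The protocol does not support that: confounding follows only if that text is carried out.

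A second reply is that baseline is measured in all arms and difference-in-difference is planned, so stable contrasts between places in services, schooling or urbanicity largely cancel over a seven-week intervention. This also stands for fixed additive differences. It does not cover place-specific trends, events or responses, and it does not supply an estimate of between-location variance.

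Third, the error rates rest on assumed ICCs and an endline-only comparison. For a change score the relevant ICC is that of change, which is not given and could be smaller. The figures are illustrations, and the structural argument does not need them.

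The figure of the Kenyan arms is not shown in the text available, so it cannot settle the matter either way.

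**Conclusion.** The contradiction is real, stands in current text and is unresolved. It should be reconciled before Kenyan recruitment. What is established is that two incompatible allocation procedures are specified for Kenya, not that the Kenyan arms are already confounded with place.

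The consequence is conditional on the Study Setting text being followed. In that case the Kenyan arm effects could not be identified, because no degrees of freedom remain for location, and the individual-level tests would be invalid. The size of the error depends on ICCs that the protocol does not give: about 17% to 56% instead of 5% over the assumed range, for an endline-only comparison and before any systematic difference between places. Peru is not affected, since all its participants come from one area.

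**What to change.** In the Kenyan paragraph of Study Setting, remove the closing words of "with the help of the Kenya National Bureau of Statistics (KNBS) as the Intervention, Contact and Control arms" that turn the locations into arms, and remove the sentence on distance and contamination. Keep the statement that locations are selected within Kwale County. Add that individuals in every selected location are randomised to all three arms by the procedure in Sampling strategy, with location as a stratum or covariate. Stratifying is feasible: if three locations contributed equally, 756 / (14 x 3) = 18 per cohort and location, or three blocks of 6.

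The cost is a one-paragraph amendment and some residual contamination, which dilutes effects towards no difference. The limit of one youth per household helps. The phone-number tracking under Data management shows which numbers use the system, but it does not stop participants from forwarding or discussing messages, and the end-intervention interviews themselves ask about sharing. Peru already accepts this risk.

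If geographic allocation is really intended, the Kenyan study must instead be described, sized and analysed as a cluster design: several locations per arm, assigned at random, a design effect in the sample size, and an analysis that respects the clusters. That is a much larger change than correcting the paragraph.

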***Participants***

For the purposes of this trial, where increased interaction with the system is anticipated and use of the phone for outcome measurement and follow-up is necessary, phone ownership is a requirement for participation. The same selection criteria will apply also to youth recruited for participation in the FGDs prior to the start of the effect assessment.

Eligibility criteria for the general ARMADILLO study is as follows:

- Youth between the ages of 13-24 (age range narrowed as needed for each site);
- Literate
- Have their own mobile phone (meaning it is primarily in their possession, and they control when and with whom they share access) and report regular use
- Have a mobile phone with them at the time of recruitment
- Report current use of text messaging

Recruitment to the FGDs preceding the trial will be purposive. Recruitment to the trial itself will be rolling over a one month period (recruitment is described more fully in the following section). Participants will be consented at their homes. Depending on the comfort level of the participant, they will continue either in their homes or be invited to meet a central location to participate in the baseline survey and be enrolled in one of the three ARMADILLO study arms. Randomization into intervention, control or Arm 3 arms will take place following completion of the baseline survey, with their seven-week interaction with the appropriate system commencing the following day. A research team member who is NOT interacting with participants will oversee the randomization of incoming phone numbers to the three arms.

In-depth interview (IDI) participants will be randomly sampled from within the pool of participants who, during their consent process, indicated they would be willing to participate in an IDI. Ten youth females and ten youth males from each country site will be selected by computer. At their end-line in-person assessment, members of the research team will invite the selected participants to participate in the IDI. Should any members indicate that they are no longer willing to participate, the computer will randomly select additional participants from the remaining pool.

In Kenya, participants will be between the ages of 18 and 24 years of age. In Peru, participants will be between 13-17 years old. The difference in age in each site is a reflection of formative phase findings and results dissemination (see summary of Stage 1 findings at the beginning of this proposal). In Kenya, the formative phase found that phone ownership dropped precipitously before age 18 (youth 17 years and below still had access to and used phones; however they were likely to be shared phones). For privacy purposes, this stage requires participants to have access to their own mobile phones; as such, the age range was set at 18-24 for Kenya. In Peru, where younger youth have access to their own mobile devices, the lower age range of participants is a direct response to recommendations from health- and education- sector stakeholders in Peru, who requested that the ARMADILLO study be directed to a younger age group – specifically, 13-17 year olds – to be more in line with national government programs to reduce adolescent pregnancy. Other eligibility requirements will not change, meaning that 13-17 year olds in Peru will still need to *have their own phone* (and indicate that they control when and with whom they share access). As indicated by young respondents in the formative phase, health-related text messages are common place in Peru; as such receipt of an SRH-related message would not be viewed with trepidation, so long as it appeared to be coming from a trustworthy source.

***Sampling strategy***

Purposive, snowball sampling will be used to recruit youth for participation in the FGDs, which will be conducted prior to the start of the effect assessment.

For the effect assessment, we will use household-based surveys and multi-stage random sampling. First, recent satellite images or a recent census will be used to identify and enumerate all of the households in the study zone. A random sample of blocks of households will then be selected. Next, the research team will carry out a census of households to enumerate all eligible (those meeting the selection criteria for this study) youth in each selected block.

Second, a member of the study team will randomly select a list of potential participants to be sampled. To minimize contamination, only one youth from each household will be able to participate in this study. The list will be a random generation of 1) the household to be sampled and 2) one individual, eligible youth to be recruited from within that household. As an equal number of males and females from each age range is desired (e.g. for Peru, 72 females aged 13 split evenly across the three arms, 72 males aged 13 split evenly across the three arms, etc), this list will be stratified by sex and age to ensure that there are adequate numbers of eligible youth for each age-sex cohort (there are 10 groups for Peru, considering an age-sex cohort range of 13-17 year-old males and females; there are 14 for Kenya, considering an age-sex cohort range of 18-24 year-old males and females)

These lists will then be recombined into one master list of eligible participants for recruitment purposes. Data collectors (none of whom will be involved in the randomization process described above) will be sent to a specific geographic area with a list of 1) the household 2) the individual within this household selected for recruitment. Upon visiting the household, the individual will be consented on the spot. In the case of Peru, parent/guardian consent will also be obtained at this point. If that individual does not wish to participate, no other eligible member of the household may be substituted. If the youth selected is not at home (and/or, in the case of Peru, the parent/guardian is not at home), we will make an appointment for a second visit.

Following enrolment, the phone number of each consented individual will be randomized into one of three arm using block randomization, with block sizes of 6, applied to the individual age-sex cohort lists. The process will continue until the sample size is achieved.

The allocation of participants into intervention, control, or Arm 3 groups (see Table 1 below) will be randomly determined but designed to achieve balance between the arms. Following enrolment of a participant into the study, an algorithm will determine to which study arm the participant’s phone number is subscribed. The subscription will be monitored either by the technology partner or a member of the research team not involved in enrolling participants. If allocated to the intervention arm or Arm 3, the participant will receive their first interaction from the appropriate system the following day. If allocated to the control arm, the participant will receive no interactions. Allocation to each arm based on the following characteristics will be assessed at least weekly to ensure balance: age, sex, and years of education.

***Study sample size***

**Table 1 Study Sample Size and a Method**

| **Stage II** | **Method** | **No. of Participants (Peru)** | **No. of Participants (Kenya)** | **Participants** |
| --- | --- | --- | --- | --- |
|  | Focus Group Discussions | 48 max (up to 6 FGDs with 6-8 participants) | 48 max (up to 6 FGDs with 6-8 participants) | In each site: 3 FGDs for males, 3 for females |
|  | Intervention arm   - In-Depth Interview | 240  10 | 252  20 | Equal numbers youth males + females |
|  | Control arm | 240 | 252 |  |
|  | Arm 3 (Contact/Push)   - In-Depth Interview | 240  10 | 252  0 |  |

For Peru, we propose a maximum of 720 participants, split evenly across intervention, control, and push arms. For Kenya, we propose a maximum of 756 participants, split evenly across intervention, control, and contact arms. A sample size of 705 participants per site will provide 80% power to detect a 10% change in mean number of myths believed from baseline to endline, assuming that baseline level of belief is 55%(30)and accounting for a dropout rate of up to 20% in each site. The sample size is calculated to allow for pairwise comparisons between all three groups. The slight increases in sample sizes in each site are to allow for the same sample size across site-specific age groups as well as for males and females.

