In both sites, formative research activities began when the initially-developed messages were vetted for comprehension, relatability, and completeness through a series of Focus Group Discussions with young people aged 15-24 in Kenya and 13-24 in Peru. FGD participants were grouped to be homogenous in sex and age range (15-17 and 18-24 in Kenya, 13-17 and 18-24 in Peru). In all FGDs, youth were asked to provide insight into the following: young people’s use of mobile phones; feedback on a series of the proposed ARMADILLO messages; perceived reactions if siblings, parents and/or significant others were to discover ARMADILLO messages on the phones of a user. In Kenya, following the completion of FGDs, a small survey of possible SRH outcomes was piloted among 250 young people as a way to plan for Stage 2.

Additionally in both sites, a series of FGDs were carried out with parents/caregivers of young people. Parents and caregivers were invited to share their thoughts on where young people learned about SRH issues; how parents handled discussing SRH issues with their children; thoughts on youth access to contraception; and perceived parent reactions if they were to discover their child accessing ARMADILLO messages. In Peru, no survey of possible SRH outcomes was completed, as by the time data collection took place, outcomes for Stage 2 were already decided.

Brief summaries of the formative stage in each site are as follows:

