***Statistical analysis***All interview data collected as part of the qualitative component of this study will be transcribed in the language it was conducted in and then (if necessary) translated into English verbatim and transferred into an electronic file containing one transcript for each data collection event. The interviewers will use these digital files and interview notes taken during data collection to write summary “topline” reports of study results. Reports will contain information on participants’ experiences and opinions using the system; recommendations for system improvement; if and with whom they shared messages; and perceived ease or difficulty in translating knowledge obtained through ARMADILLO into action (if action was desired or necessary).

The primary outcome, dispelling myths and misconceptions about contraception, will be assessed using an index of contraception myths and misconceptions(30) developed from relevant literature and the planned Focus Group Discussions. Those in the intervention arm are hypothesized to believe fewer contraception myths than those in control arm and Arm 3 and should therefore have a significantly lower index score following the intervention than they did at baseline and compared to endline assessments of the other two groups.

After assessment of the randomization of participants, if there are no differences between arms in terms of sociodemographic characteristics, differences between arms in the contraception myths index score at endline will be assessed using standard methods—comparisons of proportions(chi-square tests) and means (t-tests) between arms and difference-in-difference techniques. If the randomization was not successful, statistical adjustment with multivariable regression will be used to assess intervention impact. It is envisioned that analyses will be conducted as intent-to-treat. Separately, similar secondary analyses will be conducted on knowledge gained and attitudes shifted in other SRH domains assessed, as well as the retention of both primary and secondary outcomes over time (through the follow-up period).

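### The stated 80% power is not supported for the between-arm endline comparison that the sample size is said to serve

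*Protocol*

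**What the plan says.** The paragraph under Table 1 (Protocol, Study sample size) gives the whole justification: "A sample size of 705 participants per site will provide 80% power to detect a 10% change in mean number of myths believed". The size is chosen "to detect a 10% change in mean number of myths believed from baseline to endline", "assuming that baseline level of belief is 55" per cent and "accounting for a dropout rate of up to 20% in each site". The next sentence adds: "The sample size is calculated to allow for pairwise comparisons between all three groups". The recruitment ceilings are slightly above 705: 720 in Peru (240 per arm) and 756 in Kenya (252 per arm), to even out the age and sex groups.

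The Statistical analysis section says that "differences between arms in the contraception myths index score at endline will be assessed using standard methods": chi-square tests for proportions, t-tests for means, and difference-in-difference methods. The hypothesis there has two parts: the intervention arm's score falls below its own baseline, and it is below the endline scores of the other two arms.

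The Protocol gives no significance level, no SD for the index, no number of items and no baseline-endline correlation. It does not say whether the 10% is absolute or relative.

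**The concern.** The power sentence describes how far a score moves over time within a group. The primary objective and the main analysis compare groups with each other. For the same difference and spread, a comparison of two independent arms needs about twice as many people per arm as a one-group change measured against a fixed value. A size that suits the second can fall well short for the first.

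The effect size is also loosely defined: the outcome is an average count of myths, but the baseline is a percentage and the change is a percentage of unstated type.

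This matters for how a null result is read. In the Kenya part of the Arm 3 section, finding no difference between the intervention and contact arms would point to contact rather than content as the active element. The section on significance makes wider roll-out depend on first showing an effect. A non-significant result can bear that weight only if the between-arm power is known to be adequate.

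**Working it through.** **Inputs.** From Study sample size: 705 per site, three equal arms, 55% at baseline, 10% change, 20% dropout, 80% power. Assumed, because not stated: two-sided 5%, so 1.960 + 0.842 = 2.802, squared 7.849.

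**Completers per arm.** 705/3 = 235, and 235 × 0.8 = 188. At the ceilings: Peru 240 × 0.8 = 192; Kenya 252 × 0.8 = 201.6, about 202.

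**1. Reproducing the plan's figure as a one-group change, 55% to 45%.**
- n = 7.849 × 0.55 × 0.45 / 0.10² = 194.3. With the rounder variance 0.25, n = 196.
- 196 × 1.2 = 235 per arm, and 235 × 3 = 705.
- Power at 188: Φ(0.10 × √188 / 0.4975 − 1.96) = Φ(0.796) = 78.7%.

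So the inputs match a one-group calculation. The route to exactly 705 is inferred: it needs p = 0.5 and dropout applied as × 1.2. With p = 0.55 and n rounded up to 195, the total is 702 (× 1.2) or 732 (divided by 0.8).

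**2. Between arms, belief analysed as a proportion, 55% v 45%.**

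Power = Φ[(0.10√n − 1.96√(2 × 0.5 × 0.5)) / √(0.55 × 0.45 + 0.45 × 0.55)]

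| Completers per arm | Power |
| --- | --- |
| 188 (from 705) | 49% |
| 192 (Peru, 720) | 50% |
| 202 (Kenya, 756) | 52% |

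- Completers needed for 80%: [(1.96 × 0.7071 + 0.842 × 0.7036)/0.10]² = 391.3, so 392 per arm. That is 392/0.8 = 490 recruited per arm, or 1,470 per site.
- No dropout at all (235 per arm): 58%. One-sided 5% at 188: 62%.
- 10% read as relative (55% v 49.5%) at 188: about 19%. On that reading the one-group power is only 33%, so the stated 80% fails either way.

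**3. Between arms, index analysed as a continuous score.**

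Largest SD that keeps 80% power at 188 per arm = difference / (2.802 × √(2/188)) = difference / 0.289.
- 10 points: 10/0.289 = 34.6 points.
- 5.5 points (relative reading): 5.5/0.289 = 19.0 points.

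Over an assumed SD of 20 to 40 points, power at 188 runs from 99.8% to 68% for 10 points, and from 76% to about 26% for 5.5 points.

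**4. Detectable difference at 80% power.**
- Peru: 2.802 × √(2/192) = 0.286 SD.
- Kenya: 2.802 × √(2/201.6) = 0.279 SD.
- On the proportion scale (SD 0.4975): 0.286 × 0.4975 = 0.142 and 0.279 × 0.4975 = 0.139, about 14 points.

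**The case against.** The strongest reply is that a power near 50% treats each participant as a single yes/no answer, with an SD of about 0.497. The outcome is a multi-item index, to be compared by t-tests among other methods, and such a score usually varies less. With eight items and an assumed inter-item correlation of 0.3, the SD would be about 0.31 and the between-arm power for 10 points about 88%. This stands. A reader might infer that the trial truly has half the power it claims; the Protocol gives no SD, so that cannot be shown.

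Nor can it be said that 705 arises only from a one-group formula. A two-sample t-test with an SD of 0.346 gives 188 per arm, and 188/0.8 × 3 = 705 exactly. That SD is not printed, so this route is as much an inference as the other, but it cannot be excluded.

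The baseline-to-endline wording is also not foreign to the analysis, since a within-arm fall and difference-in-difference methods are both named. That stands as a reason to keep a within-arm target if one is wanted, but it does not supply between-arm power. On the yes/no SD with an assumed correlation of 0.5, difference-in-difference gives 49.6% and baseline adjustment 61.4% at 188 per arm. Baseline adjustment reaches 80% only at a correlation of about 0.72, which is not stated either.

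Two further steps would go too far. One is to lower the power for three pairwise tests: the Protocol states no multiplicity correction, so none is applied here. The other is to fault the plan for ignoring Stage 1, in which "a small survey of possible SRH outcomes was piloted among 250 young people as a way to plan for Stage 2". Nothing says that survey measured the myths index, Peru had no such survey, and the index is still to be built partly from planned focus groups.

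An SD might be given in a separate analysis plan that was not available for this review. The Protocol nevertheless states 80% as a fact, with inputs that do not support it for the comparison it names.

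**Conclusion.** The concern holds in this form: the 80% is worded for change over time, its stated inputs match a one-group calculation (about 79% at 188 completers), and they do not support 80% for the pairwise between-arm comparison at endline. The size of the gap depends on how the index behaves. Analysed as a proportion with an absolute 10-point difference, power is 49% to 52%. Analysed as a continuous score, 80% at 188 per arm is reached only if the SD is at most 34.6 points, or 19.0 points if the 10% is relative. All of this assumes a two-sided 5% level and 20% dropout. The fault is an unsupported power statement and an undefined effect size, not proof that the trial is too small.

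**What to change.** Keep 720 and 756 and rewrite the paragraph under Table 1:

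- State the significance level and give power for the between-arm endline contrast. For example: *with 192 (Peru) and 202 (Kenya) completers per arm, two-sided 5% and 80% power, the detectable pairwise difference in the index is about 0.29 SD and 0.28 SD.* Add the figure of about 14 points only if the outcome is analysed as a proportion.
- Say whether the 10% is absolute or relative, and on what scale.
- State the assumed SD of the index and its source, and check it against the tool pilots (25 to 30 youth per site, so only a rough check) or the baseline data. Use the Stage 1 Kenya survey only if it contained the index items.
- If a within-arm change target is kept, label it as separate from the between-arm power.

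The cost is one paragraph and no extra participants. The downside is that the stated figure may look less favourable than 80% power for a 10% change.
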